## Discussion

In a systemic review and meta-analysis, intentional segmentectomy showed non-inferiority in overall survival and disease-free survival compared with lobectomy for patients with early-stage NSCLCs (14). Intentional anatomical segmentectomy has been transformed from palliative surgery into curative treatment for those well-selected patients. Nevertheless, whether anatomical segmentectomy can be accepted as the standard of care for patients with GGO-containing early-stage NSCLC is still controversial, mostly because of lack of evidences for its benefit on pulmonary function preservation and reduction in peri-operative risks in comparison with lobectomy.

Recently, two phase III trials comparing sublobar resections with lobectomy, including Cancer and Leukemia Group B (CALGB) 140503 and Japan Clinical Oncology Group (JCOG) 0802 have released follow-up results. First of all, in both CALGB 140503 and the JCOG 0802, lesions containing GGO were not distinguished from pure solid nodules (PSN) (15, 16). However, NSCLCs with GGO component demonstrate relatively indolent biological behavior than pure solid lesions including less lymph node involvement, rare distant metastasis and better oncological prognosis (6, 17). Therefore, mixing GGO-containing nodule and SPN together will affect the results of prognosis analysis. Our trial recruits only GGO-containing lesions. And the inclusion criteria of JCOG 0802 and CALGB 140503 were based on the 7th TNM staging system, which includes patients with nodule size ≤ 2cm and solid components ≤ 2cm (cT1a-bN0M0 according to 8^th^ TNM staging). This proposed trial, however, includes GGO-containing lesions with total diameter ≤ 3cm and solid components less than 2cm, which are also cT1a-bN0M0 but pertain to the 8^th^ edition TNM staging.

Apart from the differences in inclusion criteria, the surgery approach and resection extent are different in this designed trial. No surgical approach was specified in either CALGB 140503 and JCOG 0802, which means that minimally invasive and open surgery can all be used (15, 16). Thoracic surgery has come into the era of minimally invasive surgery, which helps to reduce surgical trauma and function loss compared with traditional open thoracotomy. So, in this trial, the surgical approach is limited to minimally invasive surgery. The extent of pulmonary resection has now become the dominant factor on surgical risks and functional recovery. Unlike the sublobar group of CALGB 140503, which did not distinguish between wedge resection and segmentectomy, patients in JCOG 0802 were only divided into segmentectomy group and lobectomy group. While in JCOG 0802, there was no restriction on number of segments resected in the segmentectomy group. Segmentectomy in the GREAT study must be less than 1/2 of the corresponding lobe. If the number of segments removed ≥1/2 of the total segments of corresponding lobe, the patients will be withdrawn from the study.

Theoretically, when less lung tissue is removed, more lung function may be retained. However, pulmonary function preservation has failed to reach the expected level of 10% in the JCOG 0802 trial (16). From our previous study, if the number of segments removed ≥1/2 of the total segments of corresponding lobe, then the lung function loss of segmentectomy is similar to that of lobectomy (18). And in this previous observational study, VATS segmentectomy could reserve about 4-5% more FEV1 than corresponding VATS lobectomy. So, in the GREAT trial, segmentectomy is expected to have 5% less FEV1 loss than lobectomy.

Only with such evidences can early-stage lung cancer patients truly benefit from the advent of modern surgical techniques.

## Conclusions

If the primary endpoint shows at least a non-inferiority in 5-year RFS after surgery, minimally invasive segmentectomy can be recommended as an alternative to minimally invasive lobectomy. If the second endpoints show non-inferiority in 5-year OS along with better perioperative outcomes and/or better pulmonary function preservation of segmentectomy compared with lobectomy after the primary endpoint has reached, minimally invasive segmentectomy may become a preferred procedure for patients with GGO-containing clinical stage T1a-T1b IADCs.

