### Study endpoints

The primary endpoint is 5-year recurrence-free survival (RFS), calculated from the date of surgery to the date of cancer recurrence or patient death or the last follow-up. The secondary endpoints are 5-year overall survival (OS), perioperative outcomes and pulmonary function preservation. OS is calculated from the date of surgical resection to the date of patient death or the last follow-up. Perioperative outcomes include blood loss, operation time, morbidity rate, mortality rate, chest drain duration, length of hospital stay, and residual lung re-expansion. Pulmonary function change will be evaluated on short-term (the second day after surgical operation) and on long-term (6 month after operation) after surgery. 5% difference in FEV1 at 6 months after surgery is set as the secondary end point between the segmentectomy and the lobectomy groups. Exploratory research includes prediction of histological subtypes on preoperative imaging using artificial intelligence (AI). We also try to explore the characteristics of gene mutation status *via* next-generation sequencing (NGS) among GGO-containing early-stage NSCLCs.

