### Sample size calculation

Expected 5-year RFS is 91% according to a previous study at Shanghai Chest Hospital (6). With a one-sided alpha error of 5% and at least 80% power and a non-inferiority margin of 5% along with a drop-out rate of 5%, the sample size of this study requires 1024 patients.

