### Statistical analysis

A two-sided *p*<0.05 is set as a statistical difference. Pearson χ^2^ or Fisher’s exact test and Student t test are performed for the comparison of baseline characteristics, perioperative outcomes and the pulmonary functions. Comparisons of OS and RFS between minimally invasive segmentectomy and lobectomy groups are all estimated by Kaplan-Meier method and testified by the two-side Log-rank test. Cox proportional hazard regression model will be used to evaluate the hazard ratio of minimally invasive segmentectomy group and minimally invasive lobectomy group for OS and RFS, respectively. Subgroup analyses will also be performed by total lesion size ≤ 2cm or 2cm-≤3cm. Intention to treat analysis (ITT) will be performed for all enrolled patients. Per protocol analysis (PP) will be performed for patients who have completed the trial in compliance with the protocol.

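### The preferred-procedure claim requires 5-year OS non-inferiority, but no OS margin is stated and the only OS test named is a test of difference

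*Protocol article*

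**What the plan says.** The Conclusions, and the Discussions paragraph of the abstract, set out two levels of claim. RFS non-inferiority alone supports segmentectomy as an alternative. The stronger claim is conditional on the first: "after the primary endpoint has reached, minimally invasive segmentectomy may become a preferred procedure", provided the secondary endpoints show "non-inferiority in 5-year OS along with better perioperative outcomes and/or better pulmonary function preservation of segmentectomy compared with lobectomy".

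The parts that bear on this are:

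- **RFS** (Study endpoints) is "calculated from the date of surgery to the date of cancer recurrence or patient death or the last follow-up", so deaths are RFS events.
- **Margin** (Sample size calculation): "Expected 5-year RFS is 91% according to a previous study"; then "With a one-sided alpha error of 5% and at least 80% power and a non-inferiority margin of 5% along with a drop-out rate of 5" percent, "the sample size of this study requires 1024 patients". This is the only margin in the article.
- **OS** (Study endpoints, Statistical analysis) is a secondary endpoint with no margin, expected rate or power. It is compared by Kaplan-Meier curves and a two-sided log-rank test, with a Cox hazard ratio as the effect estimate.
- **Benefit outcomes** (Study endpoints): "Perioperative outcomes include blood loss, operation time, morbidity rate, mortality rate, chest drain duration, length of hospital stay, and residual lung re-expansion". Pulmonary function is assessed on day 2 and at 6 months, and a 5% FEV1 difference is set for the 6-month assessment.
- **Significance level** (Statistical analysis): "A two-sided *p*<0.05 is set as a statistical difference".

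**The concern.** A log-rank test asks whether two survival curves differ. A non-significant result means only that no difference was shown, and with few deaths that is a likely outcome even when mortality is materially higher in one arm. Non-inferiority needs a stated margin and an interval that excludes it. The article makes OS non-inferiority a condition of its strongest claim, then names an analysis that cannot answer the question. Someone applying the article as written has only a significant or non-significant result to go on for OS.

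The benefit condition is loose in a different way. It asks for better perioperative outcomes, better pulmonary function, or both, without saying which of the listed outcomes count or how many are needed. That could be settled after the results are known.

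What is at stake is the preferred-procedure claim. The primary RFS comparison is not affected.

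**Working it through.** **1. The margin in the article is an RFS margin.** An RFS calculation reproduces the planned size. The hazard ratio for 91% against 86% is ln(0.86)/ln(0.91) = 1.599. Schoenfeld events at one-sided 5% and 80% power are 4(1.645+0.842)²/(ln 1.599)² = 112.2. Dividing by the mean event risk (0.09+0.14)/2 = 0.115 gives 975.5 patients, and ×1.05 gives 1024.3, against 1024 stated. After 5% drop-out, 1024×0.95 = 973, or about 486 per arm.

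**2. Inputs for the OS check.** From the article: control RFS 91%, RFS margin 5 points, one-sided 5%, 486 per arm. Assumed, because the article gives no OS figure: control 5-year OS of 93, 95 or 97% (OS cannot be below the 91% RFS); a true death hazard ratio of 1.5 against segmentectomy; recurrence hazard equal in both arms; exponential, independent times.

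**3. The log-rank test alone.** Segmentectomy OS is (control OS)^1.5. Expected deaths are D = 486[(1−OS) + (1−OS^1.5)]. The chance of a non-significant result is Φ(1.96 − ln(1.5)·√(D/4)).

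| Control OS | Segmentectomy OS | Deaths | Log-rank non-significant |
|---|---|---|---|
| 93% | 89.7% | 84 | 54% |
| 95% | 92.6% | 60 | 65% |
| 97% | 95.5% | 36 | 77% |

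These figures ignore the RFS gate and so do not describe the article's rule.

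**4. Adding the RFS gate.** The extra deaths lower segmentectomy RFS to 0.91×√(control OS). The gate passes with probability Φ[(0.05 − deficit)/SE − 1.645], where SE = √{[0.91×0.09 + p(1−p)]/486} and p is segmentectomy RFS. For control OS 93%, p = 0.8776, the deficit is 0.0324 and SE = 0.0197, giving Φ(−0.755) = 22.5%. The same formula gives 40.0% at 95% and 60.5% at 97%. The joint probabilities come from simulation; repeat runs agree to within about two points.

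| Control OS | RFS gate passes | Gate passes and OS non-significant |
|---|---|---|
| 93% | about 23% | about 23% |
| 95% | about 40% | about 37% |
| 97% | about 61% | about 55% |

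Once the gate is passed, a non-significance reading of OS removes roughly 0, 3 and 6 percentage points.

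**5. Would the 5 RFS points serve as an OS margin?** On the hazard scale, 5 points equal ln(OS−0.05)/ln(OS): 1.60 at OS 91%, 2.05 at 95% and 2.74 at 97%. At control OS 97% and hazard ratio 1.5 the true deficit is 0.97 − 0.9553 = 1.47 points, with SE = √[(0.97×0.03 + 0.9553×0.0447)/486] = 0.01215. The chance of passing a 5-point margin is Φ(0.0353/0.01215 − 1.96) = 83% with a 95% interval and 90% with a 90% interval. That is laxer than the 77% for the log-rank in step 3.

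**6. The benefit outcomes.** Seven perioperative outcomes plus two pulmonary-function time points make nine. If none truly differs and one win at two-sided 0.05 were enough, the chance of at least one false win for segmentectomy is 1 − 0.975⁹ = 20.4% under independence. By simulation it is 16.6, 13.5 and 10.1% at a common correlation of 0.3, 0.5 and 0.7.

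**The case against.** The strongest reply is that the rule is gated. It applies only after RFS non-inferiority, and RFS counts deaths, so much excess mortality would stop the claim before OS is examined. This stands. A reader might infer that the preferred-procedure claim can be met by low power and chance alone; the documents do not support that, and the 54 to 77% in step 3 should not be quoted as the rule's failure rate.

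The text nowhere defines non-inferiority as a non-significant test. A Cox hazard ratio is also planned, and its interval could be compared with a margin. That is true, but no margin is given on either scale, so the article supplies no such comparison.

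A reader might also infer that a win on any one of nine outcomes is enough. The article does not say so. It speaks of perioperative outcomes in the plural, the and/or joins two domains, and 6-month FEV1 already has a stated 5% difference. The 20% is the independent case, and related outcomes such as drain duration and hospital stay bring it down. The fair criticism is that better is left undefined.

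Lastly, an article may leave a testing order, multiplicity adjustment or secondary margin to a full protocol or SAP. This largely answers the multiplicity point. It does not remove the mismatch on OS, because the article states both the claim and the test.

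**Conclusion.** The concern holds in a limited form. OS non-inferiority is a stated condition of the preferred-procedure claim, no OS margin appears, and the test named for OS cannot establish it. If non-significance were accepted in its place, the OS condition would add little to the RFS gate: with a 50% higher death hazard, the two together would still be met about 23, 37 or 55% of the time at control OS of 93, 95 or 97%. Those figures rest on the assumed OS rates, equal recurrence hazards and independent exponential times, and on the non-significance reading, which the article invites but does not state.

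The undefined benefit condition is secondary. The false-win chance of about 10 to 20% applies only if any one of nine outcomes were allowed to count. The RFS claim stands as planned. This should be corrected before the results are known, but it does not threaten the primary analysis.

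**What to change.** 1. Judge OS by the confidence interval for the 5-year difference, or for the Cox hazard ratio, against a margin justified for OS. Do not carry over the 5 RFS points without that justification. If no margin can be justified, replace OS non-inferiority in the claim with the OS estimate and its interval. The log-rank test can stay as a supporting description.
2. Name in advance the benefit outcome or outcomes that support the claim, for example the 6-month FEV1 difference already set in Study endpoints, and treat the others as descriptive. If more than one is named, state the order or the adjustment.
3. If a full protocol or SAP already holds these rules, bring the article's claim and its OS test into line with them.

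The cost is wording only, with no extra patients or visits. The downside is that the preferred-procedure claim becomes harder to reach.

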## Data availability statement

The original contributions presented in the study are included in the article/supplementary material. Further inquiries can be directed to the corresponding author.

## Ethics statement

This study has been approved by the Institutional Review Board of Shanghai Chest Hospital (IRB approval date: January 19, 2021 and approve number: IS2112) and other participant hospitals. This clinical trial has been registered at Chinese Clinical Trial Registry (ChiCTR) (Registration number: ChiCTR2000037065). The patients/participants provided their written informed consent to participate in this study.
